### Inclusion Criteria

The inclusion criteria are (1) having T2DM and being registered in the electronic CCDMS in the primary care settings (township hospitals and village clinics), (2) declaring voluntary participation in the study program with the signed informed consent form, and (3) having lived in the study village community at least 6 months.

### Exclusion Criteria

The exclusion criteria include (1) major psychiatric conditions, (2) serious diabetes complications (eg, blindness) that would impede participation in the program, (3) other serious health conditions (eg, terminal cancer), and (4) current enrollment in other research programs.

### Data Collection

Both qualitative and quantitative data will be collected in phases I and II, program development, and phase V, program evaluation. In each phase, there will be 2 stages: first, qualitative data will be collected and analyzed; second, quantitative data will be collected. Here, we describe the general methods of qualitative and quantitative data collection and analysis. The content of these assessments is described in detail in subsequent descriptions of the individual phases.

### Qualitative Data Collection

Researchers will conduct 3 focus group discussions and interviews, with 1 focus group being devoted to each of the following roles: primary care professionals, recruited participants, and peer supporters. Each focus group (6-8 participants) will be led by 2 research team members with a third team member taking notes to be checked for accuracy against audiotapes of the group meetings. Content analyses will identify the common concepts across sites and across roles (patients, professionals, peer leaders). Similar methods will be used to evaluate implementation at the end of the study, also including interviews with patients, peer supporters, and primary care providers.

### Quantitative Data Collection

The questionnaire will be developed by the research team. The questionnaire survey will be administered as face-to-face interviews for self-reported data by trained investigators.

### Quantitative Data Analyses

Social demographic data and health status of the study subjects will be presented as frequencies (percentages) for categorical variables and means (SDs) for continuous variables. Comparison of patients’ characteristics between the 3 settings will be checked by means of 2-tailed *t* tests, *χ*^2^ tests, or nonparametric equivalents. In phase V, the evaluation will include an analysis of differences at 3 months compared to baseline in self-management practice, knowledge, self-efficacy, and perception of social support.

### Ethics Approval and Informed Consent to Participate

The study was approved by the Biomedical Ethics Committee of Anhui Medical University (83220455) on October 13, 2022.

All participants are asked to provide informed consent by responding to the program survey. Participants are informed that consent includes their data being linked to primary care basic program electronic health records and agreeing to surveys and extraction of health record data at the end of the intervention during the evaluation in phase V without additional consent.

Each participant who attends the program will sign a consent form at the start of the intervention. Participants will be informed about the purpose of the study, about the course of the intervention, that it will be conducted in accordance with the study protocol, and that they are free to withdraw from the study at any time. All study data will be deidentified prior to analysis and presented only in anonymized forms.

### Implementation Development

#### Phase I: Understanding the Current Situation of Diabetes Self-Management

Understanding the current situation regarding self-management practice and identifying factors that influence patients’ self-management practice is crucial to developing the intervention program. A study questionnaire will be developed to collect patients’ demographic data, current health status, and diabetes self-management practices. Psychosocial data will be collected by using validated measurement instruments (Table 1). Self-efficacy will be measured by the Chinese Diabetes Self-Efficacy Scale (C-DSES) [32]. Social support will be measured by the Medical Outcome Study Social Support Survey (MOS-SSS) [33], and self-management practices will be measured by the Summary of Diabetes Self-Care Activities (SDSCA) [34].

**Table 1 table1:** Measurement domains and survey tools used at each data collection time point.

Variables	Quantitative measurement instruments	Baseline	3 months
Demographic and health status	Sex, age, ethnicity, education, marital status, occupation (ie, source of livelihood), cohabitants (ie, family members), length of diagnosis with diabetes, complications, and comorbidities	✓	
Psychosocial factors	CDSES^a^, MOS-SSS^b^	✓	✓
Self-management practices	SDSCA^c^	✓	✓

^a^Chinese Diabetes Self-Efficacy Scale.

^b^Medical Outcome Study Social Support Survey.

^c^Summary of Diabetes Self-Care Activities.

#### Phase II: Identify Enablers and Barriers

Health programs and interventions most likely to be successful and achieve desired outcomes are based on a clear understanding of targeted health behaviors, the factors that influence them, and the environmental context in which they occur [13]. It is critical to thoroughly understand the local primary and chronic disease care delivered by family doctors or township public health professionals in rural communities and the factors that might influence the program implementation process. Meanwhile, it is also important to understand the current social network and support for the self-management of individuals with diabetes in the rural context. It is also necessary to know the characteristics of peer group meetings or activities (eg, frequency, duration, place, content, peer leader tasks) that individuals with diabetes, professionals, and peer leaders would find helpful and feasible. The research team will develop interview and focus group discussion guidelines to gather qualitative data regarding these issues. As described above, focus groups will include individuals with diabetes, professionals, and peer supporters. The results will guide development of real-world peer support intervention activities, contents, and delivery methods.

#### Phase III: Peer Supporter Recruitment and Peer Supporter Training

Peer supporters will be recruited by recommendations from both participating patients and village clinic doctors.

##### Inclusion Criteria

The inclusion criteria are as follows: (1) having been diagnosed with type 2 diabetes for ≥1 year; (2) commitment to attending a 12-hour training session at the beginning of the program; (3) commitment to organizing activities with other patients at least 2 times every month; (4) a basic education level, including reading and writing skills; (5) having supportive, nonjudgmental communication skills; (6) willingness to lead group meetings and activities; and (7) willingness to cooperate with primary care providers, including willingness to follow guidelines for when to let primary care providers know about problems participants may be having.

##### Peer Supporter Training

Recruited peer supporters will receive 12 hours of training. Training content will include the following: (1) an introduction to the peer support intervention program in terms of purpose, contents, group activities, and peer leader roles; (2) basic knowledge and skills in diabetes self-management practices; (3) basic health communication skills; (4) the key functions of peer support promoted by Peers for Progress [28], including assisting and encouraging daily diabetes management, providing social and emotional support, linking with community resources and primary care, and providing ongoing support; and (5) guidelines and rehearsal of when and how to seek support from primary care providers regarding participant concerns or problems that are outside their competence.

A peer supporter handbook that includes training materials will be developed for use with training participants.

Because the implementation of peer support needs to be supported within its organizational setting, primary care providers will also receive training related to program implementation, their role in encouraging participation in peer support, and how they can support the peer supporters.

#### Phase IV: Peer Supporter–Led Group Meetings and Activities

Participants will be divided into groups with 6 to 10 people and assigned to peer leaders for 3 months based on how close they live to the peer leaders. Groups will be encouraged to take part in biweekly (ie, every second week) group activities with peer supporters. Peer group members will also be encouraged to organize weekly casual activities such as phone calls, WeChat voice messages, physical exercise groups, and group member family visits.

The biweekly meeting content will be based on findings from phase II and adapted and developed together with primary care providers and peer supporters. The peer group sessions will aim to achieve the following key self-management practice objectives: increasing physical activity; promoting healthy eating habits; ceasing tobacco use; reducing alcohol consumption; adhering to medication; engaging in regular clinical care and diabetes management services provided in primary care settings, such as health education classes, blood sugar and blood pressure monitoring, and physical examinations; and coping with negative emotions.

Peer supporters will also be encouraged to contact participants in their groups between the formal group sessions in order to reinforce the program objectives, update on and discuss the content of missed sessions, and encourage goal attainment and attendance at the next peer group session. These contacts may be informal through meetings within their neighborhoods.

#### Phase V: Evaluation of Feasibility and Acceptability

The aim of this last phase is to evaluate the feasibility and acceptability of the peer support approach in rural primary care settings. Quantitative outcome variables will be measured at baseline and after 3 months to evaluate program feasibility. Qualitative assessments will evaluate the feasibility and acceptability of peer support implementation.

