**Conclusions:**

Our findings will inform the design of a tailored intervention program to improve self-management among individuals with type 2 diabetes in rural primary care settings. If we find that the peer support approach is feasible and acceptable, we will develop a larger randomized controlled trial to evaluate effectiveness in multiple rural settings in the province.

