### Study Purposes

Peer support is a culturally adapted, complex intervention; evaluating such an intervention presents challenges to researchers. This study will pursue the following objectives: (1) to evaluate the feasibility and acceptability of a peer support approach to type 2 diabetes self-management in rural primary care settings; (2) to identify enabler and facilitator factors likely to influence the peer support implementation; (3) to provide primary data and evidence for developing a version of the program suitable for a randomized controlled trial in a rural primary care setting.

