##### Quantitative Evaluation

Key evaluations will be the assessment of differences between baseline and after 3 months (after completion of the peer leader program) in terms of self-management practice, knowledge, self-efficacy, and perception of social support. Additionally, changes will be compared between villages through 2-tailed *t* tests or nonparametric equivalents.

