## Discussion

### Anticipated Findings

The findings of this study will identify whether a peer support approach is an acceptable and feasible intervention in the rural primary care setting. It will provide evidence on whether the peer support program can enhance uptake, engagement, and maintenance of behaviors to reduce the risk of progression to diabetes. Findings from the study will provide invaluable information on required staff effort and key facilitators and barriers to implementing and sustaining this type of peer supporter–led group program. In addition, it will explore how the peer support self-management approach may be integrated into the NBPHSP in rural areas [4].

Generally, residents who live in the same village are familiar with each other and help each other. Group activities, such as playing mah-jongg and square dancing, are traditional in Chinese culture. This may enhance participation in the groups based on shared experiences and learning from each other. It may also contribute to participants’ knowledge and self-efficacy for self-management through group sharing and activities [35].

There is an accumulating body of studies exploring feasible and acceptable diabetes self-management programs around the world, including those that use peer support. To our knowledge, however, no previous research has examined the feasibility, acceptability, and benefits of peer support for diabetes management in primary care settings in rural China. Thus, the results of this study will provide evidence and insights for developing a peer-led support program for diabetes self-management in this important setting.

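### Phase V names pre-post score changes as its quantitative measure of feasibility, but none of those scores measures feasibility

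*Protocol article*

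**What the plan says.** All references are to the protocol article.

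- **Study Purposes.** The first objective is "to evaluate the feasibility and acceptability of a peer support approach to type 2 diabetes self-management in rural primary care settings". The third is to supply data for designing a randomized trial.
- **Phase V, opening paragraph.** "Quantitative outcome variables will be measured at baseline and after 3 months to evaluate program feasibility". The next sentence gives feasibility and acceptability to the qualitative assessments as well.
- **Phase V, Quantitative Evaluation.** "Key evaluations will be the assessment of differences between baseline and after 3 months", and these are "in terms of self-management practice, knowledge, self-efficacy, and perception of social support". Quantitative Data Analyses names the same four domains.
- **Phase I, Table 1.** The instruments repeated at 3 months are the self-efficacy, social support and self-care activity scales.
- **Phase V, Qualitative Evaluation.** Participants, peer supporters and primary care providers are asked about barriers, benefits, experiences and suggestions.
- **Abstract, Conclusions.** "If we find that the peer support approach is feasible and acceptable, we will develop a larger randomized controlled trial". Impact and Future Directions repeats this condition.

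**The concern.** A feasibility measure should show whether the program can be run: whether eligible patients agree to join, whether they stay, whether peer supporters are trained, and whether meetings happen and are attended. The plan gives the quantitative part of that task to changes in what participants do, know, feel able to do and perceive. Those changes concern possible benefit. The article itself treats effectiveness and feasibility as separate ideas in the Introduction, and it leaves the test of effectiveness to the later randomized trial.

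The protocol does more here than leave out detail. It states a purpose for a set of variables, and the variables do not fit that purpose. At stake is the quantitative half of the evidence on objective 1, which feeds the decision to develop a larger trial. Counts of patients approached and meetings attended may also be hard to recover if nobody logs them at the time.

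**Working it through.** **1. What each named variable can show.**

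| Domain compared at baseline and 3 months | What a change describes | Rate of recruitment, retention, attendance or delivery? |
|---|---|---|
| Self-management practice | Reported behavior | No |
| Knowledge | Learning | No |
| Self-efficacy | Confidence | No |
| Perceived social support | Perception | No |

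Potential Limitations and Bias acknowledges that there is no control group and that social desirability may bias the before-after comparison. The changes are therefore weak as estimates of effect too.

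**2. Score change and feasibility can point in different directions.** This is an illustration. The article gives no retention rate or effect size, so both are assumed here. It also assumes that only people with both measurements enter the comparison, which the article does not state. Let m be the number with both measurements and d the true mean change divided by the SD of the changes. The approximate probability of a significant improvement at two-sided 5% is Φ(d√m − 1.96).

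- 50% of 60 retained, m = 30, d = 0.5: Φ(2.739 − 1.96) = Φ(0.779) = 0.78.
- 50% of 45 retained, m = 22 (rounded), d = 0.5: Φ(2.345 − 1.96) = Φ(0.385) = 0.65.
- 90% of 60 retained, m = 54, d = 0: Φ(−1.96) = 0.025.

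A poorly retained program would often show a clear score gain, and a well-retained one with no true change would rarely show one.

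**3. Whether the planned size can support a feasibility measure.** Participant Recruiting expects 15 to 20 patients in each of three counties. 3 × 15 = 45 and 3 × 20 = 60, which reproduces the stated total. Assume an observed retention of 80%. The Wilson 95% interval is

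(p + z²/2n ± z√[p(1−p)/n + z²/4n²]) / (1 + z²/n), with z = 1.96.

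- n = 45 (36/45): centre 0.8427/1.0854 = 0.776, half-width 0.115, interval **0.662 to 0.891**.
- n = 60 (48/60): centre 0.8320/1.0640 = 0.782, half-width 0.100, interval **0.682 to 0.882**.

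Exact (Clopper-Pearson) intervals agree closely: 0.654 to 0.904 and 0.677 to 0.892. For observed rates from about 60% to 90%, the exact half-width is about 8 to 15 percentage points. All these intervals treat participants as independent and ignore clustering within three villages and their peer groups, so they are somewhat optimistic.

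**4. Whether the design already supplies denominators.** It does. Recruitment starts from registered patients in the chronic disease management system. Peer supporters have a 12-hour training requirement. Groups of 6 to 10 meet every second week for 3 months. With 15 to 20 people per village there would be 2 groups at the least (15/10 = 1.5, rounded up) and 3 at the most (20/6 = 3.3, rounded down), so 6 to 9 groups in all. At about 6 meetings each, that is roughly 36 to 54 scheduled meetings. With one supporter per group (an assumption) there would be only 6 to 9 supporters, so training completion will mainly be informative as a count.

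**The case against.** The strongest reply is that the plan does not rely on scores alone. The sentence after the one quoted, and the Qualitative Evaluation section, give feasibility to interviews and focus groups too, and the Abstract names both kinds of data as the evidence. **This stands.** A reader might infer that feasibility is judged only by score changes, or that the decision on a larger trial has no usable basis. The document does not support either reading.

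Other replies also stand in part:

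- No section says that a rise in scores means feasible or that flat scores mean infeasible. The divergence shown above is a risk of using this measure, not a stated decision rule.
- The analysis set and the handling of missing data are not given. They commonly belong in an analysis plan, so no completer analysis can be read into the text.
- Table 1 is captioned "Measurement domains and survey tools used at each data collection time point". Attendance sheets and recruitment logs are not survey tools, so their absence from it does not show that they will not be kept.
- "Findings from the study will provide invaluable information on required staff effort" promises information, not a count. Interviews with providers could supply it.
- Missing numeric progression thresholds could be left to a fuller protocol and are not a finding by themselves.
- The score changes have a legitimate use under objective 3, for example to estimate variability for sizing a later trial.

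None of this repairs the sentence in question. Interviews can describe why people stayed away, but they cannot give the proportion who joined, stayed or attended. A fuller document that added process measures would still need this sentence corrected.

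**Conclusion.** The point holds for the quantitative part of the feasibility evaluation. The protocol gives that task to changes in four domains, and none of the four measures feasibility. The conclusion comes from reading the sections together and needs no assumed figure. The 0.78, 0.65 and 0.025 illustrate how the two ideas can separate under assumed retention and effect. The intervals around 80% show that 45 to 60 participants can support a moderately precise process proportion. Neither set of numbers estimates harm to this study.

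Because the qualitative evaluation also informs the decision on a larger trial, and because that decision is not tied to any score result, this should be corrected but falls short of a must-fix.

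**What to change.** In Phase V (opening paragraph and Quantitative Evaluation), name these as the quantitative measures of feasibility:

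1. patients who consent, out of eligible registered patients approached;
2. peer supporters who complete the 12-hour training, out of those recruited (show the count);
3. biweekly meetings held, out of those scheduled;
4. attendance per participant;
5. 3-month assessments completed, out of participants enrolled.

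Report each with a 95% confidence interval, by village and overall. Preferably, the sponsor also sets progression criteria before Phase IV and reads them alongside the qualitative findings. Relabel the score changes as exploratory preliminary outcomes that serve objective 3, and make the same change in Quantitative Data Analyses.

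The cost is some rewording, a recruitment log and an attendance sheet for each meeting. If progression criteria are set, the study may also miss one. No extra participants or visits are needed.

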##### Quantitative Evaluation

Key evaluations will be the assessment of differences between baseline and after 3 months (after completion of the peer leader program) in terms of self-management practice, knowledge, self-efficacy, and perception of social support. Additionally, changes will be compared between villages through 2-tailed *t* tests or nonparametric equivalents.

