### Study Setting

This study will be conducted in rural communities in Anhui province. Anhui province is located in eastern China and has about 61 million people. It is divided into 3 geographic areas based on the Huai River and Changjiang River. The 3 areas are north of the Huai River, between the Huai River and Changjiang River, and south of the Changjiang River. These 3 different areas have different customs, cultures, and dietary habits. Stratified sampling will identify 1 county in each of the northern, southern, and middle regions. One township will be randomly recruited in each county. Within each township, the village that has the largest number of adults with T2DM will be selected based on the electronic management system of the local primary care system. This will result in 3 villages representing 3 areas in Anhui province with high numbers of adults with T2DM.

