### Participant Recruiting

Study participants will be identified through the Community Chronic Disease Management System (CCDMS), which was established as a national primary care package program in communities in both urban and rural areas. Primary care providers (family doctors and public health physicians) in local primary care settings (township hospitals or village clinics) will contact eligible patients to explain the purpose of the study and details of the program. Since this is an exploratory study with a new intervention approach that has never been tested before in rural Anhui Province, no formal calculation of the sample size will be performed. All patients who are registered in the CCDMS in the sampled study setting (villages) and meet the inclusion criteria will be included if they are willing to participate. An estimated 15 to 20 patients will be recruited in each county, yielding a total sample of 45 to 60 participants. Based on the recommendations of Hertzog [31], a sample of 10 to 40 people is sufficient for a pilot study using a single group to estimate the sample size for a future trial.

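### A two-group test (the t test) is named to compare continuous data across three villages; a three-group method or a descriptive report should replace it

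*Protocol article*

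**What the plan says.** Study Setting selects one county in each of three regions, one township per county and one village per township: "This will result in 3 villages representing 3 areas in Anhui province with high numbers of adults with T2DM".

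Participant Recruiting gives the size: "An estimated 15 to 20 patients will be recruited in each county, yielding a total sample of 45 to 60 participants". With one village per county, that is 15 to 20 people per village.

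Two sections then name the test:

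- Quantitative Evaluation (Phase V): "Additionally, changes will be compared between villages through 2-tailed" t tests or their nonparametric counterparts. This follows the key evaluations, which are before-after differences "in terms of self-management practice, knowledge, self-efficacy, and perception of social support".
- Quantitative Data Analyses: "Comparison of patients’ characteristics between the 3 settings will be checked by means of 2-tailed" t tests, with chi-square tests and nonparametric counterparts as the other options.

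The article names no analysis of variance, Kruskal-Wallis test or model with village as a factor. It also states no alpha and no multiplicity adjustment.

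**The concern.** The named test does not fit the number of groups. An unpaired t test contrasts two means, so with three villages it can only be run pair by pair: first against second, first against third, second against third. Each continuous variable then has three chances of a nominally significant result where one comparison was meant.

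The nonparametric option does not repair this. The strict counterpart of the unpaired t test is the rank-sum test, which is also a two-group method.

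What is at stake is the reading of a secondary result. The pilot is meant to supply evidence for a later randomized trial, and chance differences between villages would be reported more often than the nominal error rate suggests.

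**Working it through.** **Inputs**

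- Villages: 3 (Study Setting).
- Participants per village: 15 to 20 (Participant Recruiting).
- Test: two-sided t test (Quantitative Evaluation; Quantitative Data Analyses).
- Outcome domains compared for change: 4 (Quantitative Evaluation).
- Alpha: not stated. 0.05 per test is assumed, with 0.01 and 0.10 shown as a range.

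**The plan's own figure.** 3 × 15 = 45 and 3 × 20 = 60, so the stated total of 45 to 60 reproduces.

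**Number of tests.** Three villages give 3 × 2 / 2 = 3 pairs per outcome, or 3 × 4 = 12 tests if each of the four domains is counted as one outcome.

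**False-positive risk per outcome when no village differs**

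If the three tests were independent, the risk is 1 − (1 − alpha)³:

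| Assumed alpha | Independence figure | Upper bound (3 × alpha) |
|---|---|---|
| 0.01 | 1 − 0.99³ = 3.0% | 3% |
| 0.05 | 1 − 0.95³ = 14.3% | 15% |
| 0.10 | 1 − 0.90³ = 27.1% | 30% |

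The three tests share data, so the true figure is somewhat lower. A simulation with 200,000 null datasets per setting (normal data, equal variances, independent participants, alpha 0.05) gave:

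| Procedure | 15 per village | 20 per village |
|---|---|---|
| Three pairwise t tests | 12.1% | 12.1% |
| One-way analysis of variance | 5.0% | 5.0% |
| Pairwise tests only after a significant omnibus test | 5.0% | 5.0% |
| Pairwise tests, each at 0.05 / 3 = 0.0167 | 4.4% | 4.3% |

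The named method therefore carries about 12% per outcome. A three-group test brings it back to 5%.

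**Which variables are affected.** Table 1 lists several characteristics that are naturally categorical, such as sex, ethnicity, education and marital status. A chi-square test on a table with three columns, one per village, is a single test, so no pairwise problem arises. The mismatch concerns continuous characteristics, such as age if analysed as a number, and the change scores.

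**The case against.** The strongest reply is that this is a condensed article on an exploratory study with no formal sample size calculation. The village comparison is additional, and no key conclusion rests on it. An unseen analysis plan may contain a correction, and the nonparametric wording may be loose shorthand that includes Kruskal-Wallis.

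Much of this stands. It limits the severity, and it means that one can say only that no correction is named, not that none exists. It does not remove the mismatch. The article does not leave the test open: it names a two-group test for three groups, in two sections. Even on the generous reading of the nonparametric option, the parametric option remains wrong.

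A reader might infer more than the documents support:

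- **Every characteristic is affected.** No: the chi-square test already covers categorical ones.
- **The error rate is 20 to 24%.** That figure needs correlation within peer groups, with an assumed intraclass correlation of 0.05. The documents give no such value. Across assumed values of 0.01 to 0.10 the simulated rate runs from about 14% to 34%. This is also a separate problem: at 0.05, one-way analysis of variance still gave about 10 to 13%, so changing the test does not cure it.
- **The comparison is underpowered.** The article claims no power for it, so nothing is contradicted.
- **Village differences will drive regional tailoring of the later trial.** No section says so. The stated condition for going on to that trial is that the approach proves feasible and acceptable.

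**Conclusion.** The point holds in limited form. For continuous data, the article prescribes a two-group method to compare three villages. Taken literally, this raises the chance of at least one false positive per outcome from 5% to about 12%. That size assumes alpha 0.05 per test, independent participants, equal variances and no correction beyond what the article names.

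The before-after evaluations and the categorical comparisons are untouched. The correction is worth making because the stated method is wrong as written, but no key conclusion of the study depends on it.

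**What to change.** In Quantitative Data Analyses, replace t tests for continuous characteristics with one-way analysis of variance, or Kruskal-Wallis if the data are skewed. Keep chi-square tests for categorical ones.

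In Quantitative Evaluation, replace the t tests and their nonparametric counterparts with one model of the 3-month score on baseline score and village, with a single 2-degree-of-freedom test for village. Allow pairwise comparisons only if they are adjusted or run after a significant overall test.

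Preferably, go further and report village-specific mean changes with 95% confidence intervals as descriptive results only, with two notes:

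- There is one village per region. With groups of 6 to 10 people (Phase IV), 15 to 20 participants form only 2 or 3 peer groups per village. Differences therefore cannot be attributed to region.
- Neither the overall test nor simple intervals allow for correlation within peer groups, so such intervals may be somewhat too narrow.

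The cost is wording in two sections, with no extra data. The downside is that fewer nominally significant village differences will be reported.
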